## Background

Type 2 diabetes mellitus (T2DM) is a substantial health problem with a high clinical and economic burden [1, 2]. Despite a recent prognostic improvement, coronary artery disease (CAD) remains one of the leading causes of mortality in people with T2DM [3]. CAD is often severe and silent in patients with T2DM [4], prompting screening in asymptomatic individuals. Previous randomised controlled trials (RCTs) have failed to provide evidence of the effectiveness of routine CAD screening in reducing major cardiovascular events and mortality in people with T2DM at moderate to high cardiovascular risk [5–9]. However, doubts remain about T2DM patients at a very high cardiovascular risk, who can benefit from this screening strategy, but in whom trials have not yet been conducted. Despite this lack of concrete evidence, current clinical practice and guidelines recommend routine CAD screening for silent CAD in individuals with diabetes at high cardiovascular risk [10]. The widespread practice CAD screening results in significant healthcare costs due to invasive testing, revascularisation procedures, and intensified pharmacological therapies. The cost-effectiveness of routine CAD screening has not been prospectively evaluated in T2DM people. Only two economic studies based on Markov models have addressed this issue by comparing screening versus no screening strategy in Japanese and American populations [11, 12]. The results of these studies were inherently limited by assumptions inherent in the models, uncertainties in the epidemiological and cost data, and variations in health care costs between countries.

In the midst of this discrepancy between the lack of tangible evidence and clinical practice, we are conducting the Cost-effectiveness of Screening of Coronary Artery disease in patients with type 2 DIABetes at a very high cardiovascular risk (SCADIAB) study to estimate the cost-effectiveness of routine CAD screening in T2DM patients with a very high cardiovascular risk.

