### Recruitment of participants and follow‑up

Data will be extracted from 1 January 2008 to 31 December 2019. The screening period will cover the 7 years from 1 January 2008 to 31 December 2014, which will allow us to identify patient eligibility criteria. All patients identified in the SNDS databases during the pre-selection period who met the inclusion criteria will be recruited in the study from 1 January 2015 to 31 December 2015. Participants will be followed for 4 years, until 31 December 2019 (Fig. 1).

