### Screening strategies and study allocation

Each patient will be assigned into one of the two study groups according to the CAD screening strategy performed during the recruitment period. Patients who had at least one CAD screening test will be assigned to the routine CAD screening group and included at the time of the first CAD test. Patients who did not perform any CAD screening (except for the resting electrocardiogram) will be assigned to the control group, and included at the time of the resting electrocardiogram, or at the time of a medical visit (general practitioner, diabetologist, or cardiologist), whichever comes first.

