### Eligibility criteria

The key inclusion criteria are patients aged 40 years or older, with T2DM for at least 7 years, two or more additional cardiovascular risk factors (obesity, hypertension, hypercholesterolemia, or tobacco smoking), and at least one microvascular or macrovascular disease: carotid stenosis, transient ischemic attack (TIA), stroke, lower-limb peripheral artery disease, chronic kidney disease (CKD), severe diabetic retinopathy requiring laser photocoagulation, or peripheral or autonomic diabetic neuropathy. The main exclusion criteria include the presence of CAD (a history of acute coronary syndrome, coronary revascularization, angina pectoris, or unstable angina), the performance of one or more CAD screening tests, or any visit to an emergency department for chest pain resulting for admission to a cardiac intensive care unit.

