### Outcomes

The primary outcome is the incremental cost per life-year gained over 4 years in CAD routine screening group versus no screening in the perspective of French health insurance. The key secondary health economic endpoints include the cost-consequence analysis linking the total 4-year direct costs of each strategy and clinical endpoints; an analysis of budget impact for the French Insurance system to promote the routine CAD screening; and the total care consumption during follow-up. The key secondary clinical endpoints included the effects of CAD screening (versus no screening) in terms of major adverse cardiovascular events (a composite of acute coronary syndrome, coronary revascularization, or hospitalization for heart failure); all-cause mortality; major cerebrovascular events (a composite of stroke, hospitalization for TIA, or carotid revascularization); major adverse limb events (a composite of ischemic diabetic foot, lower-limb revascularization or amputation); and CKD or end-stage kidney disease (ESKD, requirement of any sustained haemodialysis or kidney transplantation). Each component of these composite endpoints will also be considered individually. Major cerebrovascular events, major adverse limb events and ESKD will be assessed during follow-up among participants without a baseline history of each condition (as appropriate). Finally, SCADIAB will also assess the frequency of routine CAD screening, expressed as the number of examinations performed yearly per individual.

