### Statistical analysis

The gross estimate of the incremental cost per life-year gained at 4 years will be conducted. High dimension propensity score will be used to balance the baseline characteristics of participants. Comparisons between study groups will be performed without adjustment; and with adjustment for confounding factors using the weighted by inverse probability of receiving treatment (IPTW). A cost-consequence analysis will be performed linking results of all direct costs, and results on major cardiovascular events. A budget impact analysis will be conducted to determine the public expenses of the spread of a routine CAD screening at 5 years from French health insurance perspective. The risk of clinical outcomes by study groups will be assessed using IPTW proportional hazards survival regression models. We will also consider the competing risk of all-cause death.

We will perform subgroup analyses by sex, age and frequency of CAD tests. Finally, a sensitivity analysis is planned to assess the interest of routine CAD screening in T2DM people with at least 2 cardiovascular risk factors without microvascular or macrovascular disease.

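### The key secondary MACE composite counts coronary revascularisation without qualifier, so procedures triggered by the screening test count as adverse events of screening

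*Protocol article*

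**What the plan says.** All references are to the protocol article.

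- **Outcomes** lists MACE among the key secondary clinical endpoints and defines it as "a composite of acute coronary syndrome, coronary revascularization, or hospitalization for heart failure". Revascularisation carries no qualifier such as urgent, and no period after the index test is set aside. The same section lists all-cause mortality as a separate endpoint and says that every component will also be looked at singly.
- **Background** says that the spread of CAD screening "results in significant healthcare costs due to invasive testing, revascularisation procedures, and intensified pharmacological therapies".
- **Screening strategies and study allocation** says that patients with a CAD test "will be assigned to the routine CAD screening group and included at the time of the first CAD test". Controls are "included at the time of the resting electrocardiogram, or at the time of a medical visit".
- **Eligibility criteria** excludes patients with CAD, described as "a history of acute coronary syndrome, coronary revascularization, angina pectoris, or unstable angina".
- **Recruitment of participants and follow-up** says: "Participants will be followed for 4 years, until 31 December 2019".
- **Statistical analysis** says that clinical outcomes will be "assessed using IPTW proportional hazards survival regression models", with death also considered as a competing risk. It adds: "A cost-consequence analysis will be performed linking results of all direct costs, and results on major cardiovascular events".

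**The concern.** Screening for silent CAD acts by finding disease and treating it, and revascularisation is one of the treatments. The article says so itself, then counts the same procedure as an adverse event when it compares screening with no screening. An excess of revascularisations in the screened group is what the strategy is expected to produce. It says nothing about whether patients fared worse.

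Two things are at stake. First, the MACE hazard ratio mixes events that screening is meant to prevent (ACS, heart-failure admission) with an event that it causes, and the two move in opposite directions. A ratio near or above 1 could mean no benefit, or a real benefit hidden by elective procedures. Second, the major cardiovascular events in the cost-consequence analysis carry the same mixture, so a payer reading that table could take procedures generated by screening for clinical failures of screening.

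**Working it through.** The article states no event rate, effect size or sample size, so there is no figure of its own to reproduce. The check has two parts.

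**1. Does the design let test-triggered procedures into the composite?**

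- Time zero for screened patients is the test, so any procedure it leads to falls inside follow-up.
- Time zero for controls is an electrocardiogram or a visit, with no CAD test to set off a procedure at entry.
- Patients with earlier revascularisation are excluded, so any procedure in follow-up is a new event.
- IPTW balances baseline characteristics. It cannot remove events that follow from the strategy.
- The per-protocol analysis drops controls who are screened later. It leaves revascularisation in the screened group as it is.
- Competing-risk handling concerns death.

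Nothing planned takes these procedures out of the composite.

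**2. How large could the push be?** All inputs below are assumptions.

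*Risk ratio.* Let a be the four-year risk of ACS or heart-failure admission, equal in both groups (no true effect), and r the share with elective revascularisation. With independent components, composite risk = 1 − (1 − r)(1 − a). Take a = 12%.

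- Screened, r = 5%: 1 − 0.95 × 0.88 = 16.4%.
- Controls, r = 0.5%: 1 − 0.995 × 0.88 = 12.4%. Ratio 1.32.
- Controls, r = 2%: 1 − 0.98 × 0.88 = 13.8%. Ratio 1.19.
- Controls, r = 3%: 1 − 0.97 × 0.88 = 14.6%. Ratio 1.12.

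With controls held at 0.5%, screened values of 2% and 8% give 13.8% and 19.0%, ratios 1.11 and 1.53. Without elective revascularisation the comparison is 12% against 12%, ratio 1.00.

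*Hazard ratio.* Let p0 be the four-year control MACE risk, h the true hazard ratio on MACE not triggered by the test, and q the share of screened patients with a test-triggered revascularisation beyond that background. Screened risk = 1 − (1 − p0)^h × (1 − q), and apparent average HR = ln(1 − screened risk) / ln(1 − p0).

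| p0 | h | q = 1% | 2% | 3% | 5% |
|---|---|---|---|---|---|
| 8% | 1.00 | 1.12 | 1.24 | 1.37 | 1.62 |
| 12% | 1.00 | 1.08 | 1.16 | 1.24 | 1.40 |
| 20% | 1.00 | 1.05 | 1.09 | 1.14 | 1.23 |
| 8% | 0.85 | 0.97 | 1.09 | 1.22 | 1.47 |
| 12% | 0.85 | 0.93 | 1.01 | 1.09 | 1.25 |
| 20% | 0.85 | 0.90 | 0.94 | 0.99 | 1.08 |

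A true 15% hazard reduction is cancelled when q = 1 − (1 − p0)^0.15, which is 1.2%, 1.9% or 3.3% at control risks of 8%, 12% and 20%.

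**The case against.** The strongest reply is that, under the intention-to-treat effect the article targets, more revascularisations are a real consequence of the strategy and would be estimated correctly. That stands. The fault lies in what the composite means, and bias in its estimation is a separate matter. The reply does not help a reader who takes a MACE ratio as harm or benefit, which is how an endpoint of major adverse events is read.

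Component reporting would show an excess of revascularisations. That also stands, but the composite ratio and the events linked to costs would keep them.

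The article is a short update of a protocol published earlier, and a qualifier on revascularisation may stand there. This limits certainty. The definition printed here has none.

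The illustration depends on how many controls have elective procedures. The article expects some controls to be screened during follow-up, and they stay in the intention-to-treat comparison. This is why the range runs down to 1.12.

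A reader might infer four stronger points that the article does not support:

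- **That MACE is the main effectiveness endpoint.** It is one of several key secondary endpoints; the primary outcome is cost per life-year gained.
- **That death is neglected.** All-cause mortality has its own endpoint, survival drives the primary outcome, and death is considered as a competing risk.
- **That a revascularisation is charged twice.** A cost-consequence analysis sets costs beside events without adding them, and an ACS admission appears in both columns too.
- **That proportional hazards is violated.** Early clustering of procedures makes this likely, but nothing here shows it, and checking the assumption can be left to the analysis plan.

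**Conclusion.** The point holds for the MACE composite and for the cardiovascular events in the cost-consequence analysis. As defined, both are pushed against screening by procedures that the article itself attributes to screening, and neither can be read as clinical harm or benefit. The effect side of the primary outcome is untouched, and the cost of revascularisation belongs on its cost side.

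The direction follows from the text; the size does not. A composite risk ratio of about 1.1 to 1.3 with no true effect on ACS or heart failure rests on an assumed 12% risk, 5% elective revascularisation in screened patients, 0.5% to 3% in controls, and independent components. The net ratio need not exceed 1: if screening prevents enough ACS or heart-failure admissions, it can stay below 1, as some cells of the table show.

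**What to change.** - Make the leading MACE composite ACS (including revascularisation within an ACS or urgent admission) or hospitalisation for heart failure. Handle death as a competing event, as already planned.
- Use this composite in the cost-consequence analysis.
- Report elective revascularisation as resource use and as a separate endpoint.
- Keep the present composite as supplementary.
- Weighted four-year cumulative incidence can be shown beside the hazard ratio, so that the timing of events is visible. Putting death inside the composite, or demoting the hazard ratio, is a matter of preference and is not needed to meet this point.

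The cost is a change of endpoint wording and a coding rule, applied to the same hospital claims, that separates ACS or urgent admissions from elective ones. The rule should be fixed before results by group are seen. The downside is fewer composite events, and so less precision, and less direct comparability with composites that include revascularisation. The supplementary analysis covers the comparability.

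### Carotid and lower-limb revascularisation count as events from the day of the index CAD test, so a procedure already planned when the test was done could be scored as an event after screening

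*Protocol article*

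**What the plan says.** Four statements in the Protocol article have to be read together.

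- **Eligibility criteria.** Besides age, diabetes duration and risk factors, a patient needs "at least one microvascular or macrovascular disease: carotid stenosis, transient ischemic attack (TIA), stroke, lower-limb peripheral artery disease" or one of several other conditions. The exclusions concern known CAD, "the performance of one or more CAD screening tests, or any visit to an emergency department for chest pain" that led to cardiac intensive care. A pending vascular procedure is not among them.
- **Screening strategies and study allocation.** A patient with a test in the recruitment period is "assigned to the routine CAD screening group and included at the time of the first CAD test". The reason for the test plays no part in the rule. A control is "included at the time of the resting electrocardiogram, or at the time of a medical visit" with a general practitioner, diabetologist or cardiologist, whichever is earlier.
- **Outcomes.** The two composites are "major cerebrovascular events (a composite of stroke, hospitalization for TIA, or carotid revascularization); major adverse limb events (a composite of ischemic diabetic foot, lower-limb revascularization", with amputation completing the second. Every component is also analysed alone. Both endpoints are assessed in participants who have no history of the condition at baseline, where appropriate. Planned and unplanned procedures are not separated, and no lag after inclusion is given.
- **Statistical analysis.** Confounding is handled by a high-dimensional propensity score on baseline characteristics, with inverse-probability weights in proportional hazards models.

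**The concern.** The eligible population includes people with known carotid or leg artery disease, some of whom may be awaiting a first procedure. If the planned procedure is the reason for the CAD test, the procedure causes entry to the screening group and is then counted as an outcome of it. That is reverse causation.

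The mechanism is not symmetrical. A similar patient operated on without a CAD test stays among the controls, and that patient's time zero is a first ECG or visit with no built-in link to the operation. Any resulting excess would fall early in the screening group and would look like harm.

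At stake are two key secondary clinical endpoints and, more sharply, their revascularisation components.

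**Working it through.** The article gives no event rate, no sample size and no breakdown of tests by indication, so there is no figure of its own to reproduce. The check is a trace through the rules, followed by an illustration on assumed values.

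**1. Trace of a hypothetical patient.** Take someone with known carotid stenosis, no coronary symptoms and no previous stroke, TIA or revascularisation, who meets the other criteria. A CAD test is done on day 0 as pre-operative work-up and a carotid procedure follows on day 21.

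- Eligible: yes, through carotid stenosis; none of the CAD exclusions applies.
- Group and time zero: screening, day 0.
- Baseline-history restriction: the conditions it names are the event endpoints themselves (cerebrovascular events, limb events, ESKD). Read literally, a stenosis without a prior event is not a history of one, so the patient stays in.
- Outcome: a major cerebrovascular event on day 21.

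If the restriction instead means the underlying arterial disease, the patient is removed and most of the problem goes. The text does not settle which is meant.

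**2. Illustration.** Assume no true effect. Let R be the 4-year risk of the composite in both arms, and q the share of screened patients whose index test was work-up for a procedure already planned. Assume no matching excess in controls and no correction by weighting.

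- Screened risk = q + (1 − q)R, so 1 − screened risk = (1 − q)(1 − R).
- Cumulative-hazard ratio = ln(1 − screened risk) / ln(1 − R) = 1 + ln(1 − q) / ln(1 − R).

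For R = 5% and q = 1%, the screened risk is 0.01 + 0.99 × 0.05 = 0.0595 and the ratio is ln(0.9405) / ln(0.95) = 1.20. For q = 2%, the screened risk is 0.069 and the ratio is 1.39.

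| R | q = 0.5% | q = 1% | q = 2% | q = 5% |
|---|---|---|---|---|
| 3% | 1.16 | 1.33 | 1.66 | 2.68 |
| 5% | 1.10 | 1.20 | 1.39 | 2.00 |
| 10% | 1.05 | 1.10 | 1.19 | 1.49 |

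**3. If controls have part of the same excess.** With share c in controls, the ratio is [ln(1 − R) + ln(1 − q)] / [ln(1 − R) + ln(1 − c)]. At R = 5%:

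- q = 1%, c = 0.5%: 0.06134 / 0.05631 = 1.09.
- q = 2%, c = 1%: 0.07150 / 0.06134 = 1.17.

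The zero-excess figures are therefore upper bounds for a given R and q.

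**4. Single components.** Background risk is lower for a component, so the same share weighs more. At R = 1% and q = 0.5% the ratio is 1 + ln(0.995) / ln(0.99) = 1.50.

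Setting q to zero gives 1.00 by construction. That says nothing about how well a 90-day window would separate planned from other procedures in the real data.

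**The case against.** The strongest reply is that the article nowhere mentions pre-operative testing. It assigns patients on a CAD *screening* test, and a definition in the full protocol might leave out tests done before surgery. The Study design section points to an earlier published protocol, and only key inclusion and main exclusion criteria are listed, so a lag rule may also exist elsewhere. This stands as far as frequency goes: the documents do not show that any index test was pre-operative. It does not remove the structural point, because time zero, group definition, event components and history restriction are all stated here and together allow the misclassification.

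Other parts of the reply also stand:

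- A high-dimensional score on claims data may capture proxies for a planned operation, and the article lists no covariates. A reader might infer that weighting cannot help; the documents do not support that. It may remove part of the bias.
- Controls can enter at a resting ECG, which may itself precede surgery, and their planned procedures count too. The assumption of no control excess is the extreme case.
- Many participants may qualify through kidney disease, retinopathy or neuropathy alone, which would keep the share small.
- The history restriction removes patients with prior events, some of whom would be candidates for a procedure.

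A reader might also infer that early procedures should be dropped from the main endpoint. The documents do not support that either. An early procedure may be a real consequence of the contact that screening creates, and no marker separating elective from emergency procedures is described.

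**Conclusion.** The concern holds in conditional form. The stated rules let a procedure that prompted the index test be counted as an event after it, and no stated safeguard clearly prevents this. If it happens, the direction is against screening.

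The size is unknown. At 5% 4-year risk with no true effect, a pre-operative share of 1–2%, no excess in controls and no help from weighting, the ratio would be about 1.2–1.4. If controls had half the excess, it would be about 1.1–1.2. All these inputs are assumptions; none comes from the article.

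A reader might go further and conclude that the two endpoints are biased, that such testing is common, or that the primary cost per life-year result is distorted. The article gives no basis for the first two. On the third, procedure costs would enter the 4-year totals, but nothing here shows by how much. The point is a cheap improvement to two secondary endpoints and does not challenge the primary analysis.

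**What to change.** In Outcomes and Statistical analysis:

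1. Keep the main count of both composites from day 0.
2. Add one pre-specified analysis, identical in both arms, that does not count carotid or lower-limb revascularisation in the first 90 days after inclusion. Stroke, TIA hospitalisation, ischaemic foot and amputation still count from day 0.
3. Report by arm the number of participants with a non-coronary vascular procedure within 90 days of inclusion. This shows directly whether the problem exists.
4. Draw no conclusion of harm or benefit on these two composites unless both analyses agree.
5. State whether the baseline condition means prior events or the underlying arterial disease.

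The added analysis uses dates that the endpoints already need and no elective or emergency marker. It costs one extra run and has slightly fewer events. It does not correct the cost outcome. If the full protocol already holds a lag rule or a rule on the reason for the test, stating it in the article would answer most of this.

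### The ESKD definition leaves out peritoneal dialysis, so some kidney-failure events are missed or dated late in this secondary endpoint

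*Protocol article*

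**What the plan says.** The protocol article, under Outcomes, names CKD or ESKD as a kidney endpoint among the key secondary clinical endpoints, and gives this definition of the second: "ESKD, requirement of any sustained haemodialysis or kidney transplantation". Two further sentences in that section bear on it. The components get their own analyses: "Each component of these composite endpoints will also be considered individually". The population at risk is restricted: "Major cerebrovascular events, major adverse limb events and ESKD will be assessed during follow-up among participants without a baseline history of each condition", with the qualifier that this applies as appropriate. No separate rule is given for recognising ESKD at baseline.

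Under Eligibility criteria, kidney disease is one of the qualifying complications: "lower-limb peripheral artery disease, chronic kidney disease (CKD), severe diabetic retinopathy requiring laser photocoagulation". The exclusions introduced by "The main exclusion criteria include the presence of CAD" concern coronary disease, earlier coronary testing and emergency visits for chest pain. Dialysis is not among those listed.

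Under Statistical analysis: "The risk of clinical outcomes by study groups will be assessed using IPTW proportional hazards survival regression models". Death is also to be considered as a competing risk. Study design says that the data come from a national claims database.

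**The concern.** The definition lists the treatments that make a participant an ESKD case, and one form of long-term dialysis is not on the list. The article describes no adjudication, and in claims data an event exists only if the codes chosen for the definition find it. A start of peritoneal dialysis would therefore not register. Because ESKD is also analysed on its own, the CKD half of the endpoint does not recover these events in that analysis. A participant who starts peritoneal dialysis and dies without changing treatment would enter the competing-risk analysis as a death without ESKD.

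At stake are the absolute ESKD incidence in both groups, the timing of some events and the precision of the ESKD comparison. The cost-consequence analysis sets direct costs beside clinical endpoints, so the cost of peritoneal dialysis would presumably be counted while its onset is not.

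**Working it through.** The article states no ESKD rate, event count, power or dialysis modality split, so there is no figure to reproduce. The check is a reading of the rule, followed by an illustration of size.

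**Step 1: apply the definition to follow-up.**
- Starts haemodialysis that is sustained, or receives a transplant: event on that date.
- Starts peritoneal dialysis and stays on it: no event.
- Starts peritoneal dialysis and later moves to haemodialysis or transplant within the 4 years: event, dated at the move and so late.

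**Step 2: size of the loss.** Let *q* be the share of first kidney replacement that is peritoneal and never switches during follow-up. This is an assumption, shown over a range of 5% to 15%.
- Captured events = (1 − *q*) × true events.
- The standard error of a log hazard ratio scales roughly with 1/√(number of events). If the loss is the same in both groups, it is multiplied by 1/√(1 − *q*).

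| *q* | Captured per 100 true events | 1/√(1 − *q*) | Rise in SE of log HR |
|---|---|---|---|
| 5% | 95 | 1/√0.95 = 1.026 | 2.6% |
| 10% | 90 | 1/√0.90 = 1.054 | 5.4% |
| 15% | 85 | 1/√0.85 = 1.085 | 8.5% |

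Participants who switch are counted late rather than lost. If *q* is read instead as the share of all peritoneal starts, these losses are upper bounds.

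**Step 3: effect on the hazard ratio.** Write λ₁ and λ₀ for the true ESKD hazards in the screening and control groups. With equal under-capture and no false events, the observed hazards are about (1 − *q*)λ₁ and (1 − *q*)λ₀. The factor cancels and the ratio stays at about λ₁/λ₀ for an uncommon outcome. Step 1 therefore costs precision and absolute incidence and does not by itself pull the ratio towards 1.

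**Step 4: the at-risk set, conditionally.** The ESKD analysis is limited to participants without that condition at baseline ("ESKD will be assessed during follow-up among participants without a baseline history of each condition (as appropriate"). Suppose baseline history is identified by the same definition. A participant already on peritoneal dialysis then has no such history, stays at risk and becomes an incident case on moving to haemodialysis or transplant. If such false events add a hazard φ to each group, the observed ratio is

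((1 − *q*)λ₁ + φ) / ((1 − *q*)λ₀ + φ),

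which lies between λ₁/λ₀ and 1. This part would dilute the contrast. The article gives nothing from which φ could be estimated, and it may be zero.

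**The case against.** The article condenses a protocol published earlier, and code lists are commonly kept in the fuller document. The word haemodialysis may also be loose usage for dialysis in general. Both points are fair. However, the article does state a definition, and that definition selects the wrong set of treatments if taken at its word. If the code list already includes peritoneal dialysis, the correction is editorial but still needed.

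A reader might infer more than the text supports in four ways:

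- **That the ESKD contrast is pulled towards no difference.** Missed events do not do this when capture is equal in both groups (step 3). Only false incident cases would.
- **That prevalent peritoneal dialysis patients are in the cohort and are counted as new cases.** The text does not say that baseline history is found by the follow-up rule alone; diagnosis coding could identify it. Only the key inclusion and main exclusion criteria are listed. CKD as a qualifying condition makes such patients possible but does not show that they are present.
- **That dialysis modality differs between groups and so biases the comparison.** Nothing in the article gives a reason why a coronary test in 2015 would change the choice of dialysis.
- **That this rule is the only way the study could see kidney harm.** The CKD component can register it whatever the modality, and care consumption and costs are not limited by the ESKD definition.

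**Conclusion.** The omission is real and stands in the text as a fixed rule. Its established consequence is limited: ESKD incidence is understated, some events are dated late, and precision falls in one part of one secondary endpoint. Under the assumed 5% to 15% peritoneal share with no switching and equal loss in both groups, 5% to 15% of events are lost and the standard error rises by about 2.6% to 8.5%, with little bias in the hazard ratio. The assumed share does not come from the article.

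Dilution by false incident cases is a further risk that depends on two things the article leaves open: that baseline ESKD is identified by the same definition, and that patients on peritoneal dialysis are enrolled. The primary outcome, cost per life-year, does not use ESKD and is unaffected. The point deserves correction because the remedy is simple.

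**What to change.** Define ESKD as any sustained dialysis (haemodialysis or peritoneal dialysis) or kidney transplantation. State that the same definition identifies ESKD at baseline, and remove those patients from the at-risk set for this endpoint.

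The cost is one change of wording and a few added procedure codes in an extraction from the same database. If ESKD has already been extracted with the narrower definition, record the change with its date and report the narrower version as a sensitivity analysis. The two results side by side would also show how many events the omission affects, which the article does not allow a reader to estimate.
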